#### **Record and report of serious adverse events/pregnancy**

Subjects should report any serious adverse events that occur after receiving the investigational drug up to 21 days after completion of the drug.

The procedures for reporting serious adverse events are as follows:

The principal investigator had to fill out a "Serious Adverse Event Report Form" and report it to the sponsor within 24 hours of learning about SAE.

The sponsor promptly evaluates the safety information received, and reports suspicious and unexpected serious adverse reactions to all participating clinical trial researchers, clinical trial institutions and ethics committees, as well as to the drug regulatory authorities and health authorities. It is also communicated to all researchers participating in clinical trials (pharmacovigilance, data management, etc.).

Sponsors may request additional information from researchers to ensure timely and accurate completion of safety reports.

The investigator must use all necessary therapeutic measures to address SAE. Any medications required to manage SAE must be documented on the subject's case report form or in combination with the eCRF.

Each SAE should be followed up to baseline or stable or lost to follow-up, and an updated report submitted to the designated person. A simple laboratory anomaly is not reported by SAE unless the investigator considers that the anomaly meets SAE standards. Laboratory abnormalities should be recorded on the "Laboratory Data" page and periodically checked by the clinical inspector.

Pregnancy: all pregnancy after administration and its outcome (spontaneous abortion, selective termination of pregnancy, ectopic pregnancy, normal delivery or congenital malformation, etc.) should be reported to the ETHICS Committee and the sponsor in writing. Male subjects also need to report their partner's pregnancy after receiving the drug.

Pregnancy itself is not reported as an adverse event or as a serious adverse event. If the pregnancy course/outcome meets SAE criteria, the investigator should report it according to SAE reporting procedures. Pregnancy outcomes should be followed up and recorded even if subjects drop out of the study.

If pregnancy occurs within 21 days of completion of dosing, the investigator should notify the sponsor within 24 hours of the pregnancy.

### **Data management**

**CRF design:** CRF shall be designed according to the test steps and flow charts stipulated in the scheme. After the preliminary draft is formed, project managers, data and statistics personnel, scheme writers and other project team members shall jointly review the CRF to conform to the scheme and comply with relevant laws and regulations, and the version control process shall be completely recorded.

**CRF filling guide:** The CRF filling guide provides detailed filling instructions for each page of the case report form and each data point according to the study protocol. Ensure that the clinical trial center has access to the CRF and its completion guidelines prior to subject enrollment, and train clinical trial center staff on the protocol, CRF completion and data submission process, which should be documented.

**CRF annotation:** Annotation CRF is the annotation of blank CRF, which records the location of each CRF data item as well as the variable names and codes in the database. All data items in CRF need to be annotated. DM review is required.

### **Database design**

The database should be set up according to the data set name, variable name, variable type, and variable length in the annotation CRF, and adhere to the standard database structure and setup as much as possible. After the establishment of the database, the database test shall be carried out, and the database test report shall be issued, which shall be signed and confirmed by the principal of data management.

**Permission Allocation**

The system administrator creates accounts and grants different permissions for different roles.

**eCRF**

The researchers shall collect the data of the subjects according to the requirements of the study protocol, and fill in the eCRF with accurate, timely, complete and standardized information according to the original data and the filling guide. Modifications to CRF data must follow standard operating procedures, leaving traces of modifications.

**Challenge sending and resolution**

The data management department shall list the detailed data verification plan, and the verification plan shall be reviewed by the programmer and the data management department and signed for confirmation if there is no objection. After the data is input into EDC, the system will check the data according to the procedures established in the data verification plan, and the data in doubt will be automatically questioned by the system.

The data that cannot be set for the system to issue questions will be sent through EDC by manual questions. Input personnel or researchers will confirm and answer manual questions and system questions, and modify the wrong data if necessary until the questions are solved. If the answer fails to resolve the query, the data manager and clinical inspector can re-query the data point, and all traces are stored in the EDC database.

**Data modification and review**

Data entry personnel or researchers can modify the data after verifying the data, and fill in the reason for modification in the system as prompted. The investigator has the authority to review all final data.

**Medical coding**

History, adverse events, and drug combinations collected during clinical trials should be coded using a standard dictionary. The standard dictionary commonly used is MedDRA, ATC. The encoded dataset should clearly record the dictionary and version used in the encoding.

**SAE consistency comparison**

All SAE-related data points in the CRF are compared with those in the PV library using the program. Inconsistent data needs to be communicated to PV personnel until there are no discrepancies.

**Data review meeting**

Before the database locked, the draft data management report and all data lists are collected, Bidders, researchers, data management and statistical analysts in the blind state under the joint audit data does not solve the problem, and according to the statistical analysis has been made to the clinical trial division and verification report serious adverse events and treatment records, such as data audit report after the meeting to be finalized data management and the crowd partition plan, etc.

**Locking and unlocking the database**

Database locking is an important milestone in clinical research. The process and time of locking should be clearly documented. Locking is revoking the right to edit the database and logging the withdrawal of the right to edit the data in the document.

If there is any modification after the database locked, an application shall be submitted, which shall be discussed and signed by the sponsor, researcher, input personnel, clinical supervisor and data management personnel, and the reasons for unlocking shall be recorded in detail.

**Save the data**

Store all collected raw data (such as CRF and electronic data) in a secure location during clinical trials. These original documents are part of the audit path that traces the original data and should be protected as strictly as the electronic audit path records any changes or backups to the database.

**Data privacy**

Data confidentiality is a basic principle that must be observed in the process of clinical research and development. Institutions involved in drug research and development should establish appropriate procedures to ensure the confidentiality of the database, including establishing and signing confidentiality agreements to regulate the behavior of relevant personnel, and establishing confidentiality systems to prevent the disclosure of the database. The data set must be encrypted before transmission. The data set and password cannot be transmitted in the same email.

**Statistical analysis**

Single point optimal subcutaneous dose test: descriptive statistical analysis; Safety and tolerability tests: descriptive statistical analysis; Pharmacokinetic test: calculate the blood concentration-time data of each subject, draw the concentration-time curve, and draw the average blood concentration-time curve. The pharmacokinetic parameters of single dose were calculated.

Pharmacodynamics test: analysis and statistics of the level changes of each indicator before and after medication; The groups were compared using a least square mean of the difference from baseline (with baseline as a covariable) and a 95% confidence interval.

**Analysis of the crowd**

Safety Set (SS) : Includes the composition of all subjects given at least one trial drug. The security analysis set is used for baseline characterization and security analysis.

PK Concentration Set (PKCS) : includes all subjects receiving the investigative drug with at least one blood Concentration data. The pharmacokinetic concentration analysis set was used for correlation analysis of pharmacokinetic concentration data.

PK Parameter Set (PKPS) : includes all subjects receiving the investigative drug with at least one pharmacokinetic Parameter. Pharmacokinetic parameter analysis set was used for correlation analysis of pharmacokinetic parameter data.

Pharmacodynamic analysis Data Set (PD Set) : includes all enrolled subjects who used the investigational drug at least once and have pharmacodynamic evaluation data after administration. Pharmacodynamic analysis datasets are used for correlation analysis of pharmacodynamic data.

**Statistical analysis method****Enrollment and completion status**

The number and percentage of subjects who were screened, enrolled, dropped off, and completed the test were calculated, respectively, and the number and percentage of subjects who were summarized for each analysis set according to the different dose groups.

**Baseline characteristic analysis**

Baseline data included demographic characteristics, laboratory tests, vital signs, and drug combinations, and were aggregated by dose group. The measurement data are described by means, standard deviation, median, maximum and minimum. For counting data, frequency and percentage are used to describe. Baseline indicators were compared between groups using population T test or Wilcoxon rank sum test and Fisher's exact probability method. Baseline analysis was performed based on the security analysis set.

**Safety/tolerability analysis**

Safety/resistance analysis included adverse events, evaluation of clinical laboratory results, and vital signs. The

safety/tolerability analysis was based on the safety analysis data set.

### **Adverse events**

Any subject receiving the investigational drug should be assessed for safety. The evaluation period shall be from the time of receiving the investigational drug to 21 days after the end of study or administration. AEs or SAEs occurring during this period shall be followed until they return to normal or stable (except for subjects who are dead, lost to follow-up, or have withdrawn their informed consent).

Adverse events were coded using MedDRA.

In this study, the adverse events (TEAE) occurred during treatment were mainly analyzed statistically. The adverse events occurred during the screening period to before the first administration were listed, but the statistical analysis of adverse events was not included.

Adverse events referred to below refer to adverse events occurring during treatment.

The incidence, number and incidence of all adverse events, drug related adverse events, serious adverse events and abortion related adverse events in each group were calculated.

According to systematic organ classification (SOC) and preferred term (PT) classification, the number of adverse events, the number of cases and the incidence of adverse events in the two groups were calculated.

A list of adverse events related to the study drug during treatment, a list of all adverse events, a list of adverse events resulting in shedding, and a list of serious adverse events were listed separately.

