## Research methods

### The main objectives of the study were as follows:

- 1.To investigate the safety and tolerability of long-acting ropivacaine injection in healthy subjects in a single subcutaneous injection of different doses;
- 2.To investigate the pharmacokinetics of long-acting ropivacaine injection during a single subcutaneous administration in healthy subjects;
- 3.The recommended single-point subcutaneous dose of long-acting ropivacaine injection was investigated.

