### Methods for increasing dose:

**1. Exploration of optimal subcutaneous dose for single point of long-acting ropivacaine injection.** The initial single-point dose of the study included five doses: 0.6mL (12mg), 0.8mL (16mg), 1.0mL (20mg), 1.2mL (24mg) and 1.5mL (30mg), totaling 5.1mL (102mg). Three healthy subjects were given five different doses at different dosing sites in a single dose.

**2. Safety, tolerability and pharmacokinetics tests of single subcutaneous administration of long-acting ropivacaine injection at different doses:** based on preclinical animal test results, 150 mg was determined as the initial dose for healthy subjects. There are five cohorts from the lowest initial dose to the maximum dose, and the dose escalation scheme is shown in the table below.

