**Table 1: Dose escalation protocol for single dose trials in healthy subjects**

| array | Dose (mg) | Number of healthy subjects (n)    |                                     |
|-------|-----------|-----------------------------------|-------------------------------------|
|       |           | Experimental group                | Control group                       |
|       |           | long-acting ropivacaine injection | ropivacaine hydrochloride injection |
| A     | 150       | 6                                 | 3                                   |
| B     | 230       | 8                                 | --                                  |
| C     | 300       | 8                                 | --                                  |
| D     | 350       | 8                                 | --                                  |
| E     | 400       | 8                                 | --                                  |
| Total |           | 38                                | 3                                   |

Positive control was set for cohort A, and no positive control was set for other dose groups. The study began at the minimum dose, with each subject receiving only one dose and only one dose cohort at a time. Safety assessments were conducted on days 7 and 21 after dosing, and the next cohort/batch trial was determined based on the results. If no significant adverse effects were observed in the maximum dose cohort (400mg), dose-escalation was not continued.

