### Termination criteria:

1.If there is any SAE associated with the investigational drug during the course of the trial, the investigator and sponsor will fully discuss the cause and determine the impact on subsequent trials before deciding whether to continue the trial.

2. According to the Evaluation Criteria for Common Adverse Events (CTCAE) (V5.0, published on November 27, 2017), if  $\geq 1/2$  of the subjects in the trial cohort have grade  $\geq$  ii adverse events or  $\geq 1/3$  of the subjects have grade  $\geq$  iii adverse events (adverse events may be determined by the investigator to be related to the test drug), the investigator and the sponsor shall discuss. Whether to terminate dose escalation;
3. If no significant adverse effects were observed in the maximum dose cohort (400mg), dose escalation was discontinued.
4. The sponsor requested a complete termination of the test;
5. The National Medical Products Administration or the ethics committee ordered the trial to be terminated for some reason.

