**Table 4 Subject Numbering table**

| Queue | Subject Number | dosage (mg) |
|-------|----------------|-------------|
| A     | 1001~1009      | 150         |
| B     | 2001~2008      | 230         |
| C     | 3001~3008      | 300         |
| D     | 4001~4008      | 350         |
| E     | 5001~5008      | 400         |

Subject numbers for each dose group will be assigned from the smallest to the largest in accordance with the order of enrollment of the subject. Subject numbers will not be omitted. Cohort A 150mg group was randomly divided into experimental group and control group, and then divided into 3 batches for the test, with 1 case in the first group and 1 case in the positive control group. In the second group, there were 2 cases in experimental group and 1 case in positive control group. In the third group, there were 3 cases in experimental group and 1 case in positive control group. The randomization statistician used SAS software to generate the randomization allocation table of

subjects in Cohort 1001-1009 in batches, according to which drugs were given to the experimental group and control group.

**Note :** (1) the random grouping of cohort A should follow the blind design, and the subjects should not know their own group; (2) The drug administration researcher and the pain measurement researcher should not be the same person.

**Administration:** After the subjects were admitted to the clinical trial ward, they were examined for vital signs (including armpit temperature, pulse, decubital blood pressure, etc.) in the morning of the next day (the day of administration) before subcutaneous administration.

**Optimal single point subcutaneous dose test of long-acting ropivacaine injection (study 1) :** 0.6mL (12mg), 0.8mL (16mg), 1.0mL (20mg), 1.2mL (24mg) and 1.5mL (30mg) were subcutaneously injected according to points 1, 2, 3, 4 and 5 marked on the abdomen of the subjects respectively.

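### The adverse-event table by organ class and preferred term is specified for two groups, but the trial has five dose groups and a control, so as worded it does not show event types by dose

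*Protocol*

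**What the plan says.** The first main objective of the protocol is "To investigate the safety and tolerability of long-acting ropivacaine injection in healthy subjects in a single subcutaneous injection of different doses". Table 1 sets out five cohorts at 150, 230, 300, 350 and 400 mg. Of the comparator, the text below that table says: "Positive control was set for cohort A, and no positive control was set for other dose groups". The text under Table 4 confirms where the randomised comparison sits: "Cohort A 150mg group was randomly divided into experimental group and control group".

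The Adverse events section under Statistical analysis method has two summary sentences in sequence. The first covers all, drug-related and serious events, plus a further category that appears to mean events leading to discontinuation, and asks for them in each group. The second covers the classification by SOC and PT and says that "the number of adverse events, the number of cases and the incidence of adverse events in the two groups were calculated". Neither sentence defines its groups. The section then asks for separate listings, including one of all adverse events.

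Elsewhere in the statistical section the dose groups are named. Enrolment and completion are to be "summarized for each analysis set according to the different dose groups". The Baseline characteristic analysis section aggregates by dose group. The Pharmacokinetic analysis section describes parameters by dose group and also by experimental and control group.

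**The concern.** The protocol does not leave the grouping of the SOC/PT table open. It states one, and the number stated does not match the design. The only two-group split that the document uses for treatment comparisons across Study 2 is experimental versus control, which heads the columns of Table 1 and is the group factor in the Pharmacodynamics analysis model. Applied to the SOC/PT table, it merges the five dose levels.

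At stake is the descriptive answer to the first main objective. In a dose-escalation study the reader wants to know whether a particular type of event becomes more frequent as the dose rises. A table with one test-drug column cannot show that. The totals asked for in each group may show it for adverse events overall, but they do not identify the event type.

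**Working it through.** **Inputs.** From Table 1: test-drug group sizes 6, 8, 8, 8, 8 and control 3. From the planned numbers under Study design: 50 subjects, of whom 41 are in Study 2, 3 in Study 1 and 6 give blank blood. The event counts below are assumptions, because the protocol gives no expected event rates for the test drug.

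**Reproducing the protocol's own counts.** 6 + 8 + 8 + 8 + 8 = 38, as in Table 1. 38 + 3 = 41, as stated for Study 2. 41 + 3 + 6 = 50, as stated for the whole trial. The design figures agree with one another, and Study 2 has 5 + 1 = 6 groups.

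**What a pooled column reports.** With p the proportion of subjects with a given preferred term at each dose, the pooled incidence is

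(6·p150 + 8·p230 + 8·p300 + 8·p350 + 8·p400) / 38.

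Each cohort of 8 carries weight 8/38 = 21.1%, and the 150 mg cohort 6/38 = 15.8%. For an event confined to one cohort of 8, the pooled percentage is the cohort percentage divided by 38/8 = 4.75, whatever the count.

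| Assumed events, all at 400 mg | By dose (exact 95% CI) | Pooled test drug (exact 95% CI) |
|---|---|---|
| 2 | 2/8 = 25.0% (3.2 to 65.1%) | 2/38 = 5.3% (0.6 to 17.7%) |
| 4 | 4/8 = 50.0% (15.7 to 84.3%) | 4/38 = 10.5% (2.9 to 24.8%) |

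The intervals are Clopper-Pearson. They overlap in both rows because the cohorts are small. What is lost is the description by dose, not a test; the Statistical analysis section makes the safety analysis descriptive in any case.

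**Different dose patterns give the same pooled figure.** Four events at 400 mg and none elsewhere give 4/38 = 10.5%. One event in each of the four cohorts from 230 to 400 mg (1/8 = 12.5% each) and none at 150 mg also give 4/38 = 10.5%. The first pattern is concentrated at the top dose and the second is level from 230 mg upwards. The pooled column cannot tell them apart.

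**Consistency with the neighbouring sections.**

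| Section | Grouping stated |
|---|---|
| Enrollment and completion status | dose groups |
| Baseline characteristic analysis | dose group |
| Pharmacokinetic analysis, parameters | dose groups, and experimental and control groups |
| Adverse events, overall categories | each group, not defined |
| Adverse events, SOC/PT | two groups, not defined |

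The SOC/PT table is the only one of these five whose stated number of groups conflicts with the design.

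**The case against.** The strongest reply is that the phrase is a slip. The English is a rough translation, and the sentence just before is visibly garbled. The objective, the enrolment and baseline summaries and the words *each group* all point towards dose columns. The pharmacokinetic section uses the dose split and the experimental/control split together, so naming two treatment groups need not rule out dose columns beneath them, and nothing in the Adverse events section says outright that doses are pooled. A statistician reading the whole section would probably tabulate by dose. Table layout is also commonly settled in the statistical analysis plan.

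Much of this stands, and it is why the point is minor. It does not remove the point. The protocol states a grouping rather than leaving it open, adjacent sentences use different terms, and nothing tells the reader which governs. An analysis plan that followed the sentence would carry the mismatch forward; one that corrected it would depart from the protocol.

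It also stands that the practical loss is limited. Dose-specific counts can be rebuilt from the listing of all adverse events. The escalation criteria work within a cohort, since they count how many "of the subjects in the trial cohort have grade" II or III events and above. Safety is reviewed before the next cohort or batch is dosed. Injection-site irritation, laboratory values and vital signs have their own assessments or summaries.

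**Conclusion.** The point holds as a minor correction. The SOC/PT sentence names two groups in a study with six. On its only plausible two-group reading, experimental versus control, it gives no event-type incidence by dose. That falls short of the first main objective and departs from the by-dose summaries elsewhere in the same section. The size rests on that reading and, for the percentages, on assumed counts: a factor of 4.75 for an event confined to one cohort of 8. If the phrase is only a slip, nothing is lost once it is corrected.

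A reader might infer four stronger things, which the document does not support.

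- *That the table covers cohort A alone, 6 versus 3, and omits the 38 − 6 = 32 test-drug subjects at higher doses.* The randomised split makes this thinkable. But safety is analysed on the Safety Set, which "Includes the composition of all subjects given at least one trial drug", and the Adverse events section opens by requiring a safety assessment of everyone dosed.
- *That a dose-related reaction would go unnoticed, or that escalation would be misdirected.* Review during the trial is by cohort, and the listings keep the dose information.
- *That the undefined term in the sentence on overall events is a second error.* It is detail not yet given, and it can properly be read as dose groups.
- *That the Study 1 subjects are mishandled.* The protocol says "Three healthy subjects were given five different doses at different dosing sites in a single dose", and they meet the Safety Set definition. Not saying where they appear in the table is a layout matter that an analysis plan may settle.

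**What to change.** In the Adverse events section under Statistical analysis method, replace the words *in the two groups* with: in each dose group (150, 230, 300, 350 and 400 mg) and the control group. A pooled test-drug column may be added beside these.

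The cost is one phrase and a wider table. No new data, subjects or visits are needed. The small downside is that the test-drug columns have 6 or 8 subjects and the control column 3, so the percentages are imprecise; showing counts with denominators beside them deals with that.
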